## Abstract

**Background:**

Functional dyspepsia (FD) is a common health problem currently without any optimal treatments. Acupuncture has been traditionally sought as a treatment for FD. The aim of this study is to investigate whether acupuncture treatment helps improve symptoms of FD.

**Methods/design:**

A two-center, randomized, waitlist-controlled trial will be carried out to evaluate whether acupuncture treatment improves FD symptoms. Seventy six participants aged 18 to 75 years with FD as diagnosed by Rome III criteria will be recruited from August 2013 to January 2014 at two Korean Medicine hospitals. They will be randomly allocated either into eight sessions of partially individualized acupuncture treatment over 4 weeks or a waitlist group. The acupuncture group will then be followed-up for 3 weeks with six telephone visits and a final visit will be paid at 8 weeks. The waitlist group will receive the identical acupuncture treatment after a 4-week waiting period. The primary outcome is the proportion of responders with adequate symptom relief and the secondary outcomes include Nepean dyspepsia index, EQ-5D, FD-related quality of life, Beck’s depression inventory, state-trait anxiety inventory questionnaire, and level of ghrelin hormone. The protocol was approved by the participating centers’ Institutional Review Boards.

**Discussion:**

Results of this trial will help clarify not only whether the acupuncture treatment is beneficial for symptom improvement in FD patients but also to elucidate the related mechanisms of how acupuncture might work.

**Trial registration:**

ClinicalTrials.gov Identifier: NCT01921504.

## Background

Functional dyspepsia (FD) is a functional gastrointestinal disorder without any structural lesion [1]. It is reported that the prevalence of FD ranges from 8% to 23% in Asia [2], and in particular, FD is claimed to affect 25% of the South Korean population [3]. Though FD is not a life-threatening disease, FD patients suffer from a poor quality of life (QoL), which is regarded as an economic burden on society [4].

Although various treatments for FD, such as proton pump inhibitors, prokinetic agents, tricyclic antidepressants, and antinociceptive agents are available [5-9], many FD patients turn to other complementary and alternative therapies largely due to a lack of satisfactory relief by these treatments [10].

Acupuncture treatment is one of the most sought-after therapeutic modalities in complementary and alternative medicine. It has been frequently used to treat symptoms of FD [11] largely based on the following rationales: firstly, acupuncture is well known to relieve pain in various conditions [12] and may help reduce epigastric pain or burning sensation [4]; secondly, previous studies have shown that manual acupuncture and electro-acupuncture modulates gastric/duodenal motility through the activation of sympathetic efferent nerve fibers or vagal nerve fibers [13]; finally, since patients with FD have been reported to have higher levels of psychological distress or depression than healthy subjects [14,15], the anxiolytic or antidepressant effects of acupuncture have been utilized to minimize worsening of FD symptoms [16-18].

However, previous studies have reported inconsistent findings of the clinical benefit of acupuncture treatment for FD [4,19]. Nevertheless, these studies have been criticized for adopting relatively sub-optimal acupuncture treatment, i.e., three times a week for 2 weeks [19,20], or testing a less generalizable treatment regimen, i.e., daily acupuncture treatment for 4 weeks [4]. According to a systematic review by Zhu [21], the acupuncture treatment for FD lacks high-quality evidence. Hence, it was addressed that randomized clinical trials corresponding with the CONSORT statement and STandards for Reporting Interventions in Clinical Trials of Acupuncture (STRICTA) recommendations have to be implemented to evaluate the efficacy of acupuncture for FD. In addition, considering the questions which have been raised so far on the adequacy of various sham acupuncture controls [22,23], care should be taken before simply adopting any available sham devices or procedures in the early phase.

Given that FD is now regarded as a complex disorder of which the pathophysiological mechanisms are inconclusive [24], various factors are likely to come into play. Among them, ghrelin, an orexigenic peptide, has been shown to play an important role in gastric motility, food intake, and potential gastroprotection against acute gastric mucosal injury [25,26]. However, it is yet to be studied whether ghrelin is associated with the mechanisms of acupuncture treatment in patients with FD [27,28].

Taken together, we felt the need to properly test whether acupuncture treatment would help symptom improvement in FD patients and, subsequently, the related mechanism. Therefore, we propose a two-center, randomized, waitlist-controlled trial investigating the effectiveness of acupuncture for symptom improvement in patients with FD and to assess whether the change in ghrelin secretion is associated with acupuncture treatment.

## Methods/design

### Objectives

The aims of this study are to: i) assess the effect of acupuncture treatment on patients with FD in comparison with waitlist group with respect to adequate symptom relief and ii) to elucidate whether ghrelin level is associated with clinical effect of acupuncture.

### Hypothesis

We hypothesize that eight sessions of acupuncture treatment over 4 weeks will improve symptoms of FD.

### Design

A two-center, randomized, waitlist-controlled trial will be conducted at the Kyung Hee University Korean Medicine Hospital and Kyung Hee University Hospital at Gangdong in Seoul, Korea from August 2013 to January 2014. The flow of the entire trial is shown in Figure 1.

**Figure 1 F1:**
[figure not shown]
Flow of the study.

### Inclusion and exclusion criteria

#### Inclusion criteria

Participants who meet the following criteria will be included:

i) Individuals between the ages of 18 and 75 years, able to read and write Korean language

ii) Individuals who meet the Rome III FD criteria

iii) Individuals who check more than four points on the visual analogue scale (VAS; 0, no symptom disturbance at all; 10, very severe) for dyspeptic symptoms

iv) Individuals who have normal esophagogastroduodenoscopy results within a year and have been diagnosed with FD by a specialist consultation

v) Individuals who receive no other treatments during the study

vi) Individuals who voluntarily agree with a study protocol and sign a written informed consent

#### Exclusion criteria

Participants who report any of the following will be excluded:

i) Individuals who have peptic ulcer or gastroesophageal reflux disease confirmed by esophagogastroduodenoscopy

ii) Individuals who have obvious signs of irritable bowel syndrome

iii) Individuals who have alarm symptoms (weight loss, black or tar stool, or dysphagia)

iv) Individuals who have serious structural disease (disease of heart, lung, liver or kidney) or mental illness

v) Individuals who have had surgery related with the gastrointestinal tract, except for appendectomy more than six months ago

vi) Individuals who are pregnant or breastfeeding

vii)  Individuals who are taking drugs which might affect the gastrointestinal tract; a minimum wash-out period of two weeks is required before participating in the trial

viii)  Individuals who are HIV-positive

ix) Individuals who have a problem of malabsorption or maldigestion

x) Individuals who have difficulties in attending the trial (e.g., paralysis, serious mental illness, dementia, drug addiction, time constraint, severe disorder in vision or hearing, illiteracy)

xi) Individuals unwilling to sign the informed consent

xii)  Individuals with other diseases that could interfere with acupuncture treatment, e.g., clotting disorders or leukopenia, pace-maker, epilepsy, or anticoagulant therapy

### Recruitment

Patients who have participated in our previous studies will be contacted to ask if they are interested. Advertisements will be put on notice boards and homepages of the hospitals, advertising boards on the subway trains, and local newspapers. Obtaining consent will be carried out by the investigators with the principle of informed consent, which consists of information, decisional capacity, and voluntarism. The participants will sign two written informed consent forms, general consent form and additional consent provisions for collection and use of their human biologic material, and go through the screening test. The model consent form and other related documentation given to participants can be provided upon request.

### Randomization

After signing an informed consent and undergoing the screening test, the participants in each hospital will be randomly assigned to one of the two groups using block randomization. Random numbers will be generated using the PROC PLAN of SAS 9.2 (SAS Institute Inc., Cary, NC, USA) by an independent statistician and sent to the Acupuncture and Meridian Science Research Center (AMSRC) at Kyung Hee University where the each randomization number will be put in a sequentially numbered opaque envelope and remain sealed by an administrative staff who is otherwise not involved in the study.

Once a participant passes the screening test, the investigator will call the AMSRC staff who is responsible for this randomization process to give her the hospital name, and the initial and screening number of the participant. The AMSRC staff will then immediately fax a document containing a unique random number and participant group allocation. This feedback document will be kept in the trial master file.

### Intervention

#### Acupuncture treatment

Detailed information on acupuncture treatment is summarized based on the revised STRICTA recommendations [29] in Table 1. The acupuncture treatment procedures were designed to reflect the real clinical setting.

**Table 1 T1:** **Acupuncture treatment details based on the STRICTA 2010 checklist**[29]

**Item**	**Detail**
**1. Acupuncture rationale**	**1a) Style of acupuncture**
	- Manual acupuncture based on traditional meridian theory.
	**1b) Reasoning for treatment provided, based on historical context, literature sources, and/or consensus methods, with references where appropriate**
	- Partially-individualized manual acupuncture treatments based on the traditional meridian theory, clinical experience, and consensus by the experts in acupuncture and FD.
	**1c) Extent to which treatment was varied**
	- Partially-individualized acupuncture treatment, i.e., fixed points plus optional points according to symptoms.
**2. Details of needling**	**2a) Number of needle insertions per subject per session (mean and range where relevant)**
	- From 9 to 19.
	**2b) Names (or location if no standard name) of points used (uni/bilateral)**
	- Nine fixed points: LI4, ST36, LR3, and SP4 (bilateral) and CV12 (unilateral).
	- Optional points according to individual symptoms: GB21, SI14, PC6, EX-HN5, and ST34 (bilateral).
	**2c) Depth of insertion, based on a specified unit of measurement, or on a particular tissue level**
	- From 5 to 30 mm.
	**2d) Response sought (e.g., de qi or muscle twitch response)**
	- ‘De qi’ sensation.
	**2e) Needle stimulation (e.g., manual, electrical)**
	- Manual stimulation: needle rotation with thumb and index fingers at 3 Hz.
	**2f) Needle retention time**
	- Fifteen minutes.
	**2g) Needle type (diameter, length, and manufacturer or material)**
	- A sterilized stainless steel needle (0.25?×?40 mm, Dongbang Acupuncture Inc., Bundang, Sungnam, Korea).
**3. Treatment regimen**	**3a) Number of treatment sessions**
	- Eight treatment sessions in both acupuncture and waitlist groups.
	**3b) Frequency and duration of treatment sessions**
	- Twice weekly for 4 weeks, 15 minutes for each session.
**4. Other components of treatment**	**4a) Details of other interventions administered to the acupuncture group (e.g., moxibustion, cupping, herbs, exercises, lifestyle advice)**
	- No other interventions during the study period allowed.
	**4b) Setting and context of treatment, including instructions to practitioners, and information and explanations to patients**
	- University hospitals.
	- Participants will be informed about acupuncture treatment in the study as follows: “In this study, acupoint for FD will be used based on traditional Korean medicine textbook and FD-related reports.”
**5. Practitioner background**	**5) Description of participating acupuncturists (qualification or professional affiliation, years in acupuncture practice, other relevant experience)**
	- Korean Medicine Doctors who have a license and at least 3 years of experience in gastrointestinal disorders. They went through 10 hours of training and simulation to ensure that they are able to provide identical acupuncture treatment in accordance with a pre-defined protocol.
**6. Control or comparator interventions**	**6a) Rationale for the control or comparator in the context of the research question, with sources that justify this choice**
	- A waitlist group will be adopted as a first step before we move on to a sham controlled trial.
	**6b) Precise description of the control or comparator. If sham acupuncture or any other type of acupuncture-like control is used, provide details as for items 1 to 3 above.**
	- Participants in the waitlist will not receive acupuncture treatment after randomization for 4 weeks, during which period, there will be six telephone visits. After this waiting period, they then will receive twice weekly acupuncture sessions for 4 weeks in the same manner as in the acupuncture group.

CV, Conception Vessel; EX-HN, Extra acupoint of Head and Neck; FD, functional dyspepsia; GB, Gallbladder; LI, Large Intestine; LR, Liver; PC, Pericardium; SI, Small Intestine; SP, Spleen; ST, Stomach; STRICTA, STandards for Reporting Interventions in Clinical Trials of Acupuncture.

In this trial, partially-individualized manual acupuncture treatments based on the traditional meridian theory and consensus by the experts in acupuncture and FD, will be given. The number of inserted needles per participant per session ranges from 9 to 19. The acupuncture points consist of basic points and optional points. All participants will be given needling at nine fixed points: Large Intestine 4, Stomach (ST) 36, Liver 3, and Spleen 4 bilaterally, and Conception Vessel 12 unilaterally. The optional points include Gallbladder (GB) 21, Small Intestine (SI) 14, Pericardium (PC) 6, Extra acupoint of Head and Neck (EX-HN) 5, and ST 34. These optional points will be selected according to the participant’s symptoms such as headache (EX-HN5), shoulder or back pain (GB21, SI14), nausea and/or vomiting (PC6), and heartburn or epigastric pain (ST34). Two additional Ah-Shi points in the medial scapular region will be allowed in case of shoulder or back pain.

The questions about symptoms related to optional points will be asked to participants by the clinical research coordinator to minimize the bias induced by contact between doctor and participant.

A sterilized stainless steel needle (40 mm length and 0.25 mm diameter; Dongbang Acupuncture Inc., Bundang, Sungnam, Korea) will be used. The depth of needle insertion will be from 5 mm to 30 mm and needle manipulation to achieve ‘de qi’ sensation will be performed. The acupuncture needles will be retained for 15 min.

All acupuncture treatments will be provided by the same Korean Medicine Doctor at each hospital, who will have undergone 10 hours of training and simulation to ensure that they are able to provide identical acupuncture treatment in accordance with a pre-defined protocol.

#### Acupuncture group

The participants in the acupuncture group will receive eight acupuncture sessions over 4 weeks. After the treatment period, they will be followed-up for 3 weeks with six telephone visits to collect adequate relief data and they will pay a final visit at 8 weeks. No other interventions during the study period will be allowed and a diary will be collected.

#### Waitlist group

The participants in the waitlist group will not receive acupuncture treatment after randomization for 4 weeks, during which period there will be six telephone visits once or twice a week. After this waiting period, they will then receive twice weekly acupuncture sessions for 4 weeks in the same manner as in the acupuncture group. No other interventions during the study period will be allowed and a diary will be collected.

#### Primary outcome

The primary outcome is the proportion of responders (PR) [30], which is the proportion of subjects who answer “yes” to more than half of adequate relief questions in the treatment period. Participants are asked to answer the following question at each visit during the treatment period (twice weekly for 4 weeks), at each telephone visit during the waiting period, and at the follow-up visit: “After the last visit, have you had adequate relief of your stomach pain or discomfort?” Responders are defined as participants reporting adequate relief for at least 50% of the study period, i.e., responding “Yes” more than four times out of eight. The proportion of responders will be compared between the acupuncture group and the waitlist group.

#### Secondary outcomes

##### Nepean Dyspepsia Index – Korean version (NDI-K)

The Nepean Dyspepsia Index (NDI) [31,32] is a reliable and valid measure of QoL in FD. The NDI originally contains 42 items designed to measure symptoms and health-related QoL in dyspepsia. We will use the Korean version of NDI (NDI-K), as validated in 2004 by Lee et al. [33], consisting of two sections about symptom-based questions and QoL. In this trial, symptom-based questions such as period, severity, and degree of distress of 15 symptoms will be evaluated at baseline, 4 weeks, and 8 weeks.

##### EuroQol-5 Dimensions (EQ-5D)

EuroQol-5 Dimensions (EQ-5D) [34,35] is one of the standardized preference-based instruments as a measure of health-related QoL. This self-report questionnaire consists of an EQ-5D index and an EQ-5D VAS. To assess the index-based values (utilities), the three-level version of EQ-5D on five dimensions (mobility, self-care, usual activities, pain/discomfort, and anxiety/depression) will be used. EQ-5D VAS records an individual’s rating for his/her current health-related QoL state on a standard vertical 20 cm VAS (similar to a thermometer) where the endpoints are labelled as ‘best imaginable health state’ at the top and ‘worst imaginable health state’ at the bottom, respectively. A validated Korean version of EQ-5D will be administered in our study [36]. This measurement will be carried out at baseline and after 4 and 8 weeks.

##### Costs

FD-related costs will be assessed using medical records and a pre-defined questionnaire to collect direct medical cost including clinic or hospital care and prescription or over-the-counter drugs, and direct non-medical costs including formal/informal care and transportation costs. Time lost for doctor visits and absence from paid work due to FD will be taken from patients’ self-reported questionnaires. Direct medical costs used in this study, such as acupuncture costs, will reflect the real world situation in Korea from a societal perspective. Additional resource consumption data from patients will be measured at baseline and after 4 and 8 weeks.

##### Functional Dyspepsia-Related Quality of Life (FD-QoL) questionnaire

The FD-QoL questionnaire is composed of four categories of diet (five items), daily activity (four items), emotion (six items), and social functioning (six items). Higher total sum scores of FD-QoL indicate worse QoL. The questionnaire to be used in this study was validated among Korean FD patients in the previous study [37] and the measurement will be done at baseline, 4 weeks, and 8 weeks.

##### Beck’s Depression Inventory (BDI)

The Beck’s Depression Inventory (BDI) [38] is one of the most widely used instruments for measuring the severity of depression. This is a self-report inventory and consists of 21 multiple-choice questions. The participants will complete the BDI at baseline, 4 weeks, and 8 weeks.

##### The State-Trait Anxiety Inventory (STAI)

The State-Trait Anxiety Inventory (STAI) [39] is a psychological inventory to evaluate the degree of anxiety based on a 4-point Likert scale and consists of 40 items on a self-report basis. The STAI measures two types of anxiety – state of anxiety (20 items; anxiety triggered by a specific event) and trait of anxiety (20 items; anxiety derived from personal characteristic). Higher scores are positively correlated with higher levels of anxiety. This measurement will be completed at baseline, 4 weeks, and 8 weeks.

##### Ghrelin measurement (total ghrelin and deacylated ghrelin)

Ghrelin is mostly secreted by endocrine cells in the oxyntic mucosa of the stomach [40,41] and is present in the peripheral circulation as two subtypes: acylated and unacylated [42]. Its physiologic functions include regulating food intake [43,44] and secretion of gastric acid [45], accelerating gastric emptying [46], and stimulating gastric motility [47,48]. In our study, approximately 6 mL of whole blood, 3 mL each for total and unacylated ghrelin, will be collected on an empty stomach at baseline and at 4 weeks. The total and unacylated ghrelin assay will be performed using the commercially available radioimmunoassay and enzyme-linked immunosorbent assay kits.

### Sample size calculation

Sample size was determined based on our clinical experience and previous reports where the waitlist group achieved approximately 28% of the PR in patients with irritable bowel syndrome [49]; in our study, we expected that 60% of the participants on the acupuncture arm would achieve adequate relief for over a half of the study period while up to 25% of those on the waitlist arm would achieve such an outcome. Generally, a level of significance of α?=?0.05 and a power of 1–β?=?0.80 were used. The sample size in this trial was estimated according to the following formula where (p_t_?+?p_c_)/2:

$$\begin{array}{l} n=\;{\left(Z_{a/2}\sqrt{2\bar{p}\left(1-\bar{p}\right)}+\;\mathrm{Z\beta}\sqrt{p_{t}\left(1-p_{t}\right)+p_{c}\left(1-p_{c}\right)}\right)}^{2}\\ \;/{\left(p_{t}-\;p_{c}\right)}^{2} \end{array}$$

Assuming p_t_?=?0.6 (p_t_: the effect of the acupuncture group) and p_c_?=?0.25 (p_c_: the effect of the waitlist group), a sample size of *n*?=?30.1 is calculated to achieve 5% of significance level and 80% power. Considering an assumed dropout rate of 20%, a total of 76 participants will be needed with 1:1 allocation to each group (38 participants per group). First, both centers will respectively recruit 30 patients each. After that, the remaining 16 patients will be recruited and randomized competitively to include 76 patients in total.

### Statistical analysis

A statistical analysis will be performed by an independent statistician who is blinded to group allocation using SPSS 21.0 (IBM SPSS Statistics, New York, USA). Our independent statistician will have an access to the final dataset which will be kept locked so that investigators will have limited access. All data will be presented as means and standard deviations or number (%), and all analyses will be based on an intention-to-treat principle. For intention-to-treat analysis, the last observation carried forward rule will be applied. The statistical significance level will be set at 0.05 (two-sided), with the 95% confidence intervals.

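### Last observation carried forward does not suit a responder outcome counted over eight answers: for anyone who leaves in the first half, the last answer alone would set the result

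*Protocol article*

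**What the plan says.** The Statistical analysis section commits every analysis to the intention-to-treat principle and then gives one rule for missing data: "For intention-to-treat analysis, the last observation carried forward rule will be applied". The primary outcome is not exempted, and the article does not say whether the rule fills individual relief answers or the final responder status.

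Under Outcome measures, Primary outcome, each participant is asked repeatedly over the four-week period about relief since the last visit. A responder is someone who says Yes "more than four times out of eight"; the same sentence also describes the cut-off as at least half of the period. Table 2 schedules no relief question at baseline, so the first answer comes after treatment or waiting has begun.

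The Sample size calculation section states the expected loss: "Considering an assumed dropout rate of 20%, a total of 76 participants will be needed with 1:1 allocation to each group". The Discussion concedes that doctors and participants are not blinded.

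**The concern.** Carrying a value forward is usually pictured for an outcome read once, at the last visit. Here the outcome is accumulated over eight readings. Filling the empty places with the last reading multiplies that reading and can swamp the rest. A participant who says No, No, Yes and then leaves ends with 6 Yes of 8 and is a responder on the strength of one answer.

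In an open-label trial with a waitlist, people may leave for different reasons in the two arms, so their last answers may differ by arm for reasons unrelated to relief over four weeks. With about one participant in five expected to leave, the primary comparison would then depend partly on the filling rule.

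The rule also gives no class to someone who leaves before answering at all.

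The questionnaires, collected at baseline, 4 and 8 weeks, raise a related problem. Copied baseline or week-4 values would enter the repeated-measures analysis as if they had been observed. In the waitlist arm, a week-4 value copied to week 8 is a pre-acupuncture value standing in for a visit scheduled after acupuncture.

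**Working it through.** **Inputs.** From Sample size calculation: responder rates 0.60 (acupuncture) and 0.25 (waitlist), 80% power, 20% dropout, 38 per arm. From Statistical analysis: two-sided 0.05. From Outcome measures, Primary outcome: eight answers, cut-off either at least 5 Yes (the count) or at least 4 Yes (the share).

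**The plan's own figure.** The mean rate is (0.60 + 0.25)/2 = 0.425. Then n = [1.960 × √(2 × 0.425 × 0.575) + 0.842 × √(0.60 × 0.40 + 0.25 × 0.75)]² / 0.35² = 30.1, as stated. Dividing by 0.8 gives 37.6, so 38 per arm and 76 in total. The expected loss is 0.2 × 38 = 7.6, about 8 per arm.

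**What the rule does to the count.** Suppose a participant gives k answers and leaves, and the other 8 − k places take the last answer.

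- Last answer Yes: the count is at least 1 + (8 − k). For k ≤ 4 this is at least 5, so the participant is a responder under either cut-off.
- Last answer No: the count is at most k − 1. For k ≤ 4 this is at most 3, so the participant is a non-responder under either cut-off.

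Listing every Yes/No sequence gives the same counts for both cut-offs:

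| Answers before leaving | Sequences where the class equals the last answer |
|---|---|
| 1 | 2 of 2 |
| 2 | 4 of 4 |
| 3 | 8 of 8 |
| 4 | 16 of 16 |
| 5 | 31 of 32 |
| 6 | 57 of 64 |
| 7 | 99 of 128 |

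**Scenario A: no true difference.** Assume completers respond at 25% in both arms, 20% leave each arm early, half of acupuncture dropouts end on Yes, and 10%-20% of waitlist dropouts do.

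- Acupuncture: 0.8 × 0.25 + 0.2 × 0.50 = 0.30.
- Waitlist: 0.8 × 0.25 + 0.2 × 0.10 = 0.22, up to 0.8 × 0.25 + 0.2 × 0.20 = 0.24.

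Summing exact binomial probabilities at 38 per arm, the uncorrected χ² test rejects in about 13% (0.30 v 0.22) to 9% (0.30 v 0.24) of trials, against a nominal 5%.

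**Scenario B: true 35-point difference, non-informative dropout.** Assume independent answers with constant probability. The chance of at least 5 Yes in 8 equals 0.60 when the per-answer probability is 0.603, and 0.25 when it is 0.445. Someone who leaves after one to four answers is classed by the last answer, so becomes a responder with probability 0.603 or 0.445.

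- Acupuncture: 0.8 × 0.60 + 0.2 × 0.603 = 0.60.
- Waitlist: 0.8 × 0.25 + 0.2 × 0.445 = 0.289.

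The difference falls from 0.35 to 0.31. Power at 38 per arm falls from 88.6% (no dropout) to 79.2%.

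**Outer bounds.** With completers at 0.60 v 0.25 and 20% early dropout, last answers of all Yes in acupuncture and all No in waitlist give 0.68 v 0.20. The reverse gives 0.48 v 0.40.

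**The case against.** Several stronger conclusions are tempting, and the article does not support them.

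- **That one answer decides every dropout's result.** It does not. From the fifth answer on, earlier answers can override the last, and after seven answers 93 of 128 sequences are settled with no filling at all.
- **That the analysis is biased.** The direction and size depend on when and why people leave, which the article does not say. Waitlist participants also have a reason to stay, since they receive acupuncture after four weeks.
- **That the analysis is not intention-to-treat.** The article states that principle, and the rule keeps everyone with at least one answer. Only participants with no answer are in doubt. Their number is unknown, nothing says they would be excluded, and a fallback may stand in a full protocol or analysis plan that is not shown.
- **That the rule adds 6 to 8 spurious points.** This gap in Scenario A is an error only if there is no true effect, or if the dropouts are truly non-responders. With completers at the planned 0.60 v 0.25, the same dropout assumptions give 0.8 × 35 + 0.2 × (30 to 40) = 34 to 36 points, against 35 planned.

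Two further objections stand. The enumeration assumes that single answers are filled, which the article leaves open. Multiple imputation is also not the only defensible replacement: with about 8 dropouts per arm it may be unstable, and it usually assumes missing at random.

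None of this rescues the stated rule for participants who leave in the first half of the period.

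**Conclusion.** The concern holds as a point about fit. Last observation carried forward is the stated rule for all analyses. Applied to single answers, it hands the responder status of anyone leaving after one to four answers to the last answer, and nearly always does so after five. This is true under either reading of the cut-off and needs no assumption about the data. The rule also leaves participants with no answer unclassified.

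The effect on the arm difference is not determined. With 20% dropout it could be a false gap of 6 to 8 points under Scenario A, a loss of about 4 points under Scenario B, or close to nothing. These are scenarios resting on assumed dropout behaviour, not forecasts. For the questionnaires, the defect is that copied values are treated as data; its size cannot be computed from the article.

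The change should be made because it is cheap and removes an avoidable dependence of the primary result on the filling rule.

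**What to change.** Replace last observation carried forward as follows.

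1. **Primary outcome.** State one rule that classifies all 76 participants, including those with no answer. One option is multiple imputation of the missing relief answers by arm, using the observed answers, baseline VAS and hospital, with responder status derived afterwards. Keep the imputation model small, given about 8 dropouts per arm.
2. **Sensitivity analysis.** Count every unanswered question as no relief, in both arms.
3. **Continuous outcomes.** Use a mixed model for repeated measures on observed values, with nothing carried forward.

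The change needs no new data and no extra participants. It costs a little more analysis work, slightly wider intervals, and a missing-at-random assumption that the sensitivity analysis must probe. That sensitivity analysis has less power. In the limiting case where every dropout becomes a non-responder, the rates are 0.8 × 0.60 = 0.48 and 0.8 × 0.25 = 0.20, and power at 38 per arm is 74.1%. It should be read as a check on the primary result, not as a second test to be passed.
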